### Trial and data management

Personal data will be handled confidentially and data collection will comply with the EU General Data Protection Regulation and the Dutch Act on Implementation of the General Data Protection Regulation. Participants will be assigned a study identification number, which will be used on all research documents. This number is stored in a master file, only accessible to the principal investigator, co-investigators and study monitor. The web-based application Castor EDC will be used for coded data entry and storage [41]. All the questionnaires are conducted digitally with the use of this platform and automatically stored. Data concerning the usage of the online platform Minddistrict are stored within the online platform itself. Neuropsychological assessments and informed consent forms will be stored in locked file cabinets at the Department of Medical Psychology of the Amsterdam UMC. All magnetoencephalography and MRI files will be stored on a network server at the hospital. Data will be stored until 15 years after the completion of the project. This study will be subject to independent on-site monitoring in accordance with the Dutch Federation of University Medical Centers quality assurance advice regarding research involving human subjects.

### Sample size calculation and Bayesian design

A multicentre trial by our group on a 12-week BCBT intervention for fatigue among severely fatigued patients with advanced cancer showed that 14 weeks after baseline, patients in the intervention group reported significantly lower CIS-fatigue scores compared to patients receiving care as usual (−7.22, 97.5% CI −12.73 to −1.72; *p*=0.003, Cohen’s *d*=0.72) [25]. Based on these outcomes we anticipated a standardized effect size (Cohen’s *d*) of 0.7 on the CIS-fatigue.

The required number of patients was calculated as 40 per arm. As we expect a maximum of 20% to drop out before the second assessment at 14 weeks after baseline, we aim to recruit a maximum of 100 patients. The trial uses a Bayesian two-arm multistage trial design, where repeated evaluations for efficacy and futility take place after the second assessment CIS-fatigue scores have been observed for 20, 25, 30 and 35 patients in each arm. Frequentist operating characteristics of the trial were evaluated by means of simulation. In the Bayesian model we assumed CIS-fatigue scores to be normally distributed and weakly informative conjugate normal-gamma priors will be used. Parameters for the prior distribution were chosen such that the impact of the prior on the posterior means for the mean and standard deviation for the CIS fatigue scores were negligible. The empirical one-sided significance level was 2.4% and below the desired one-sided significance level of 2.5%. Empirical power was 79% when the standardized effect size was 0.7 (Cohen’s *d*). The expected sample size is 27.4 per arm (54.8 in total) in case of equal means and 31.5 (63 in total) in case standardized effect size is 0.7. A standard two-arm trial without interim analyses would require 43 patients per arm, accounting for 20% drop-out.

### Termination for efficacy or futility

Both at the interim analyses and final analysis, efficacy will be concluded when the posterior probability that the mean CIS-fatigue scores for BCBT are lower than the mean CIS-fatigue scores for usual care exceeds 99%. If this happens at an interim analysis, the trial is stopped and efficacy is concluded. The trial will be stopped for futility as soon as an interim analysis shows that the predictive probability of concluding efficacy at the end of the trial drops below 10%.

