### Primary and secondary endpoints

The primary outcome measure is the CIS-fatigue score at the second assessment, 14 weeks after baseline. The eight CIS-fatigue items are rated on a seven-point Likert scale with a total score ranging from 8 to 56. A score ≥ 35 indicates the presence of severe fatigue [36]. See Additional file 1 for an overview of all primary, secondary and exploratory assessments.

The set of secondary outcomes consists of several symptoms, quality of life and level of functioning measured by questionnaires at baseline, after 14 weeks and in follow-up, including depression, HRQOL and anxiety.

Neurocognitive functioning is tested using a standardized clinical test battery that is normally used for clinical care to evaluate preoperative and postoperative cognitive status. It consists of widely used standardized psychometric instruments with published normative data, such as the Stroop Color Word Test [56] and the Rey Complex Figure Test [57].

Furthermore, data about the usage of the online platform are collected, such as the number of logins, start and finish date of a module, completion date of the diaries and the amount of time spent on the platform. Therapists will register the time they invest per patient. Patients’ expectations of intervention outcome [58] and their satisfaction with the intervention and the platform [59] will be assessed before and after the intervention, respectively.

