### Statistical analysis

The final analysis is conducted on an intention-to-treat basis. Efficacy of the intervention will be concluded based on the posterior probability as outlined in the previous paragraph. Cohen’s *d* will be calculated as an effect size for CIS-fatigue scores where multiple imputation will be used to deal with missing second measurements. Sensitivity analyses will be performed to assess the robustness of the standardized effect size under different imputation strategies.

In addition, analysis of covariance (ANCOVA) will be performed for the secondary outcomes of the second assessment, with the baseline score on the dependent measure as covariate and group allocation as the fixed factor. A *p*-level of 0.05 will be used. Longer-term follow-up effects will also be tested using ANCOVA, with the baseline score on the dependent measure as covariate. Different tumour types will be added to the model as covariates. Cohen’s *d* will be calculated as effect sizes for the secondary outcomes.

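### The primary efficacy and futility decisions use a valid but unadjusted comparison of week-14 CIS-fatigue means, although a pre-randomisation CIS-fatigue score is available for every patient

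*Protocol article*

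**What the plan says.** The endpoint is a follow-up score, not a change score: "The primary outcome measure is the CIS-fatigue score at the second assessment, 14 weeks after baseline" (Primary and secondary endpoints).

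The decision quantity at the interim and final analyses is "the posterior probability that the mean CIS-fatigue scores for BCBT are lower than the mean CIS-fatigue scores for usual care", which must exceed 99% (Termination for efficacy or futility). The trial stops for futility when the predictive probability of final success falls below 10%.

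The model is given under Sample size calculation and Bayesian design: "In the Bayesian model we assumed CIS-fatigue scores to be normally distributed and weakly informative conjugate normal-gamma priors will be used". The prior is described through its effect on a mean and a standard deviation. No regression term appears.

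The Statistical analysis section keeps the same rule at the end: "Efficacy of the intervention will be concluded based on the posterior probability as outlined in the previous paragraph". It then assigns adjusted analyses to the other outcomes. For the secondary outcomes, "analysis of covariance (ANCOVA) will be performed for the secondary outcomes of the second assessment, with the baseline score on the dependent measure as covariate"; for later follow-up, "Longer-term follow-up effects will also be tested using ANCOVA, with the baseline score on the dependent measure as covariate".

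CIS-fatigue is measured at screening, before randomisation, as an entry criterion (score of 35 or more). It is measured again at a baseline assessment, which takes place after randomisation and before treatment.

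**The concern.** The primary decision is the only efficacy comparison in the article for which baseline adjustment is not specified, yet the covariate is collected anyway. In a linear model, adjusting for a pre-treatment score with correlation r to the outcome multiplies the residual variance by about 1 − r². Leaving it out keeps variance in the posterior that could be removed at almost no cost.

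Power is stated as 79%, and the Discussion names low inclusion as a challenge and presents the Bayesian design as a way to enrol only as many patients as needed. Precision that comes without extra patients serves that aim. It also gives some protection at the first look, at 20 per arm, where chance differences between the arms in starting fatigue are largest.

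**Working it through.** **Inputs from the article.** Looks at 20, 25, 30 and 35 per arm and a final analysis at 40; efficacy if the posterior exceeds 0.99; futility if the predictive probability is below 0.10; d = 0.7; 20% drop-out; 1:1 allocation. Stated results: power 79%, one-sided level 2.4%, expected sample size 27.4 per arm under equal means and 31.5 at d = 0.7.

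**Assumed.** A vague prior, because the prior parameters are not given; d = 0.7 on the raw week-14 SD (the cited difference and effect size imply 7.22/0.72 ≈ 10.0 points); r from 0 to 0.6.

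**Step 1: reproduce the stated design without a covariate.** With n per arm, D the difference in means in favour of BCBT and s the pooled SD:

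- Posterior probability = T(D / (s√(2/n))), where T is the t distribution function on 2n − 2 degrees of freedom.
- Predictive probability of success at 40 per arm = T((D − c·s√(2/40)) / (s√(2/n − 2/40))), where c is the 99th percentile of t on 78 degrees of freedom.

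Simulating 100,000 trials per scenario gives power 78.9% (stated 79%) and one-sided level 2.34% (stated 2.4%). Expected evaluable patients per arm are 21.97 under the null and 25.64 at d = 0.7. Divided by 0.8 for drop-out, these are 27.5 and 32.1, close to the stated 27.4 and 31.5. The fixed-sample figure also reproduces: 34 per arm, and 34/0.8 = 42.5, so 43. The article's figures are therefore those of a model with no baseline covariate.

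**Step 2: add the pre-treatment score.** D becomes D − b·(difference in mean pre-treatment score), where b is the pooled within-arm slope. The residual variance comes from the regression on 2n − 3 degrees of freedom, and the standard error includes the uncertainty in b. Looks and thresholds are unchanged; 60,000 trials per row. Expected enrolment is 2 × evaluable per arm / 0.8.

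| r (assumed) | Power at d = 0.7 | One-sided level | Expected enrolment at d = 0.7 | Evaluable per arm matching 40 unadjusted, 40(1 − r²) |
|---|---|---|---|---|
| Unadjusted | 78.9% | 2.3% | 64.1 | 40 |
| 0 | 78.5% | 2.3% | 64.5 | 40 |
| 0.1 | 78.9% | 2.4% | 64.3 | 39.6 |
| 0.2 | 79.8% | 2.3% | 64.1 | 38.4 |
| 0.3 | 82.3% | 2.4% | 63.3 | 36.4 |
| 0.4 | 85.4% | 2.3% | 62.3 | 33.6 |
| 0.5 | 88.8% | 2.4% | 61.1 | 30.0 |
| 0.6 | 93.4% | 2.4% | 58.8 | 25.6 |

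Simulating the covariate from a truncated, skewed distribution changes the power figures by less than 1 point. At d = 0.5, power is about 50% unadjusted and about 53%, 57%, 62% and 69% at r = 0.3, 0.4, 0.5 and 0.6.

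**Step 3: chance imbalance at the first look.** At 20 per arm the SD of the difference in mean pre-treatment score is √(2/20) = 0.32 SD. A difference of 0.5 SD or more in either direction occurs in about 11% of trials, half of them favouring BCBT. It reaches the outcome multiplied by r: at r = 0.3 it shifts the week-14 contrast by 0.3 × 0.5 = 0.15 SD.

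**The case against.** **Nothing is in error.** The unadjusted comparison is unbiased under randomisation, and its level and power are as stated. This stands, and it sets the limit of the point.

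**The model could be detailed elsewhere.** A condensed article may leave covariates to a fuller document, and a separate normal-gamma model per arm is an inference. But the article states the decision quantity and the model, names adjustment only for other outcomes, and reports operating characteristics that reproduce without a covariate. That is a stated choice, not an omission.

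**The gain may be small.** This stands. No r is given, and entry at 35 or more on a scale of 8 to 56 restricts the range of the covariate. As an illustration, assume bivariate normal scores and a cut at the top 40%, borrowing the Background's figure for severe fatigue in long-term low-grade glioma survivors. Unrestricted correlations of 0.3, 0.4 and 0.5 then become about 0.17, 0.24 and 0.31, and the gain is roughly 1 to 3 points. The screening score is also further in time from week 14 than the baseline score.

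**Tempting stronger readings.** A reader might infer that the week-14 result (unadjusted) and the follow-up result (adjusted) cannot be compared. They can: in a randomised trial with a linear model both target the same mean difference and differ only in precision. A reader might also infer that a chance imbalance passes in full into a stopping decision. It passes only in proportion to r, and the simulated level already averages over such imbalances.

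**Conclusion.** The point holds as an avoidable loss of efficiency in the primary decision model. It is not a bias and not a type I error problem.

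Against 79% unadjusted, adjusted power at d = 0.7 ranges from about 78% (r = 0) to about 93% (r = 0.6). The gain is about 1 point or less up to r = 0.2, and about 3, 6 and 10 points at r = 0.3, 0.4 and 0.5. The level stays at about 2.2–2.5%. Expected enrolment falls only by about 1–3 patients at r = 0.3–0.5, so the benefit is mainly power.

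These figures rest on an assumed r, a vague prior, a linear relation, and d = 0.7 on the raw week-14 SD. If the source effect size was standardised on a baseline-adjusted SD, which the article does not say, unadjusted power would be below 79%. The possible loss is under 1 point and the possible gain is several, so the change is worth making even though r is unknown.

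**What to change.** Before the first look, replace the two-mean model with a conjugate Bayesian linear regression (normal-inverse-gamma prior) of week-14 CIS-fatigue on arm and the screening CIS-fatigue score. Use the screening score, not the baseline assessment, because the latter follows randomisation in an unblinded trial. Apply the existing 99% and 10% rules to the arm coefficient at all looks. Re-simulate the one-sided level, power and expected sample size over a range of r that includes values near 0, and restate them.

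The cost is a protocol amendment, one rerun of the simulation, and under 1 point of power if r is near 0. No new data or patients are needed, and the closed-form posterior is kept. At submission of the article twelve patients were enrolled, well short of the 20 per arm needed for the first look, so at that time the change could still precede any interim decision.

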### Statistical analysis

The final analysis is conducted on an intention-to-treat basis. Efficacy of the intervention will be concluded based on the posterior probability as outlined in the previous paragraph. Cohen’s *d* will be calculated as an effect size for CIS-fatigue scores where multiple imputation will be used to deal with missing second measurements. Sensitivity analyses will be performed to assess the robustness of the standardized effect size under different imputation strategies.

In addition, analysis of covariance (ANCOVA) will be performed for the secondary outcomes of the second assessment, with the baseline score on the dependent measure as covariate and group allocation as the fixed factor. A *p*-level of 0.05 will be used. Longer-term follow-up effects will also be tested using ANCOVA, with the baseline score on the dependent measure as covariate. Different tumour types will be added to the model as covariates. Cohen’s *d* will be calculated as effect sizes for the secondary outcomes.

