## Discussion

Fatigue is the most prevalent symptom of brain tumour patients and is linked to several symptoms, such as depression, sleep disturbances, anxiety, and decreased HRQOL. Patients with diffuse glioma have poor survival and high symptom burden, so the quality of survivorship should be an important factor of treatment. A significant part of care for quality of survivorship is symptom management [63]. Cognitive behavioural interventions seem promising in reducing fatigue severity based on their effectiveness in cancer survivors and palliative cancer patients.

One of the challenges in brain tumour research is the low rate of patient inclusion. Multiple provider reported barriers could explain these low rates, including concerns about the costs and time for patients, frequent hospital visits, suboptimal discussion of possibilities of trial participation and barriers in completing follow-up [64, 65]. This trial tackles some of these barriers by using a blended care intervention with telemedicine limiting visits and travel time. The recruiting clinicians are part of the research team, ensuring a good workflow for patients and clinicians. A researcher will coordinate recruitment, limiting the time spent on recruitment by clinicians. Also, by randomizing patients to a WLC group in the trial, we overcome a potential barrier for patients in enrolling in a trial compared to trials with a care as usual control group. If recruitment is slower than expected after a year, we will include more hospitals for recruitment.

Furthermore, this trial incorporates a Bayesian trial design with a flexible number of patients to be included, ensuring that only the number of patients actually needed to show relevant results will be included. Our trial will include patients with different types of diffuse glioma. This can result in different survival rates, rates of tumour recurrence and dropouts. Subgroup analyses per tumour type may help to explore potentially varying treatment effects.

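### The 24-week ANCOVA leaves out the 14-week score; if run on observed scores it loses precision and can be biased, and one longitudinal model would use data already collected

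*Protocol article*

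**What the plan says.** The Statistical analysis section of the protocol article sets out three things.

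- Secondary outcomes at week 14: "analysis of covariance (ANCOVA) will be performed for the secondary outcomes of the second assessment", with the baseline score as covariate and group as fixed factor. "A *p*-level of 0.05 will be used".
- Outcomes at week 24: "Longer-term follow-up effects will also be tested using ANCOVA, with the baseline score on the dependent measure as covariate". Tumour type is then added as a covariate. The 14-week score is not in the model.
- Missing data: "multiple imputation will be used to deal with missing second measurements". This sentence concerns Cohen's d for CIS-fatigue. No method is named for missing secondary or 24-week scores.

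The same section opens with "The final analysis is conducted on an intention-to-treat basis". The abstract gives primary and secondary outcomes at baseline, 14 and 24 weeks. Under Assessments and procedures, the 24-week assessment is limited to web questionnaires, so the hospital-based neurocognitive tests have no 24-week value. That section also says that patients who drop out or are withdrawn are still asked for both later assessments. On the mix of glioma types, the Discussion remarks: "This can result in different survival rates, rates of tumour recurrence and dropouts".

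**The concern.** Week 24 is the last assessment, and waiting-list patients are offered the therapy after it. The 24-week comparison is therefore the only controlled evidence on whether an effect lasts.

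Some loss between weeks 14 and 24 is likely. Eligibility asks for an expected survival of only three months, patients can be withdrawn for progression, and the article budgets drop-out (at most 20%) only up to week 14. How a patient felt at week 14 may influence whether the 24-week questionnaires are completed. Participants are unblinded, and by then one arm has finished therapy while the other is still waiting for it, so that influence could differ between arms.

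An ANCOVA on baseline alone, run on those with a 24-week score, cannot correct for this, because it ignores the one collected measurement that carries the information. It also discards that measurement's contribution to precision, which matters more if the trial stops at an early look.

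**Working it through.** **The plan's own figures.** None is given for the 24-week tests. Those for the primary design reproduce. The article states "Empirical power was 79% when the standardized effect size was 0.7"; a simulation with vague priors (200,000 runs per scenario) gives 79.0%, with type I error 2.34% against the stated 2.4%. A fixed t-test needs 34 per arm, and 34/0.8 = 42.5, rounded up to the stated 43. Likewise 40/0.8 = 50 per arm, or 100. The primary design is not in question.

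**Inputs from the article.** 40 evaluable per arm; d = 0.7 at week 14; 0.05 level (taken as two-sided); SD of CIS-fatigue implied by 7.22/0.72 = 10.03, so about 10 points.

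**Assumptions, not in the article.**
- The effect is still 0.7 at week 24, or zero.
- Correlations are 0.4 (baseline to week 14), 0.7 (week 14 to week 24) and 0.4 (baseline to week 24).
- All 14-week scores are observed, and 10-30% are lost after week 14.
- The odds of loss change by a factor e per SD of the 14-week score. Those doing worse are lost more often, except that in the opposite-by-arm case waiting-list patients doing better are lost more often.

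Effects are signed so that positive means benefit.

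**Formulas.** Let β be the slope of the 24-week on the 14-week score given baseline and group, γ the group coefficient in that same regression, and α the baseline-adjusted group difference at week 14.

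- ANCOVA on observed scores: γ + β·α(retained patients)
- Longitudinal estimate: γ + β·α(all patients)
- Bias of the ANCOVA: β·[α(retained) − α(all)]

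Here β = (0.7 − 0.4×0.4)/(1 − 0.4²) = 0.54/0.84 = 0.643, and γ = 0.70 − 0.643×0.70 = 0.25.

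**Results, true 24-week effect 0.70** (300,000 per arm):

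| Loss depends on the 14-week score | ANCOVA, 10% loss | 20% loss | 30% loss | Longitudinal |
|---|---|---|---|---|
| equally in both arms | 0.673 | 0.656 | 0.646 | 0.70 |
| in BCBT only | 0.742 | 0.778 | 0.816 | 0.70 |
| oppositely by arm | 0.798 | 0.888 | 0.980 | 0.70 |

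At 20% loss the bias is −0.044, +0.078 and +0.188 SD, or about −0.4, +0.8 and +1.9 CIS points. Working back, α among retained patients is (0.656 − 0.25)/0.643 = 0.63, (0.778 − 0.25)/0.643 = 0.82 and (0.888 − 0.25)/0.643 = 0.99, against 0.70 in all patients. The standard error with 40 per arm is about 0.23, so the two larger biases are roughly one third and four fifths of a standard error.

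The direction can reverse. With dependence in the waiting-list arm only and a true benefit of 0.60, ANCOVA gave 0.51-0.53 at 20% loss and 0.46-0.50 at 30%; the longitudinal estimate was 0.60.

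**No true effect.** Equal dependence: no bias, rejection 4.6-5.0%. BCBT only: bias 0.05 to 0.15, rejection 6.0-8.4%. Opposite by arm: bias 0.10 to 0.28, rejection 7.5-20.1%. The longitudinal model rejects in 4.0-5.0% throughout.

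**Sensitivity.** For the three tabulated patterns, with correlations from 0.3/0.6/0.3 to 0.5/0.8/0.5 and 10-30% loss, ANCOVA bias runs from −0.05 to +0.29 SD. The longitudinal estimate stays within 0.01 SD.

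**Precision without bias.** With 20% loss completely at random and d = 0.7, the SD of the estimate is 0.228 for ANCOVA and 0.218 for the longitudinal model. The variance ratio is (0.218/0.228)² = 0.91, and power is 83% against 86%. With equal dependence it is 81% against 87%.

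**Where the argument stops.** If loss depends on baseline only, neither method is biased at week 24. At week 14, with loss depending on baseline and arm, ANCOVA gives 0.702 against a true 0.70.

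**The case against.** The strongest objection is that the article never says the ANCOVAs use observed scores only. ANCOVA can follow imputation, and the team already plans imputation and sensitivity analyses for CIS-fatigue. Missing-data detail for secondary outcomes may sit in a full protocol or analysis plan that is not shown. This stands: silence on missing 24-week scores is no fault, and the bias here is conditional on an observed-case analysis. What remains is the stated choice of a 24-week test that ignores the 14-week score.

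A reader might also infer a conflict with the intention-to-treat statement. The text does not support that. Analysing by allocated group is compatible with ANCOVA, and a conflict arises only if observed-case handling is assumed.

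Nor should the criticism be extended to the 14-week secondary outcomes. Baseline-adjusted ANCOVA is valid there when loss depends on baseline and arm, and a longitudinal model adds information only for patients who miss week 14 but return at week 24.

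The Discussion links differing drop-out to tumour type, not to the 14-week score or to arm, and tumour type is already a covariate. Continued assessment after drop-out, a questionnaire-only follow-up and the promise of therapy after follow-up should all limit loss. These points make a large bias less likely but do not exclude it.

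Finally, the simulated loss depends only on the 14-week score, so the longitudinal model is bound to look unbiased. That is fair: it shows what the model corrects, not that it corrects everything.

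**Conclusion.** The point holds for the 24-week questionnaire outcomes, conditionally. The stated 24-week ANCOVA omits a measurement that is already collected. Run on observed scores, it is less precise even with random loss (83% against 86% power at 20% loss). It is biased when loss after week 14 depends on the 14-week score: slightly and toward zero if the dependence is equal across arms, and materially, in a direction not known beforehand, if it differs by arm. Post-week-14 loss, correlations, loss mechanism and the 24-week effect are all assumptions.

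The documents do not support the stronger reading that the 24-week result will be biased, or that a longitudinal model would be unbiased whatever the cause of loss. The efficacy decision rests on the 14-week posterior probability and is unaffected. This is a worthwhile, inexpensive improvement to secondary evidence, not a threat to the trial's main conclusion.

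**What to change.** For each questionnaire outcome measured at baseline, 14 and 24 weeks, estimate the 24-week group difference from one mixed model for repeated measures. Include group, time, group by time, baseline score, baseline by time and tumour type, with unstructured covariance and all randomised patients who have at least one post-baseline score. ANCOVA after multiple imputation with the 14-week score in the imputation model is an acceptable equivalent; if that is already intended, one sentence saying so is enough.

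The 14-week secondary ANCOVAs can stay, as can the analysis of the neurocognitive tests, which have no 24-week value.

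The cost is a change of analysis wording and slightly more modelling; no new data are needed. The model relies on loss being at random given the observed scores, so it does not correct loss driven by unobserved ones, for example progression after week 14. The 24-week report should say so.
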